### Sample size

Based on the results of a pilot study with 171 patients, we found a standard deviation (SD) of 1.2% in HbA1c and, given that that the mean SD in literature is around 2%, we used an SD of 1.5% to calculate the sample size. Considering an intra-class correlation of 0.05 [18] and an average of 10 participants per group, we calculated that we needed 277 participants per study arm to detect a clinically relevant difference of 0.5% in HbA1c levels at 12 months, with 80% power, with p-value of 0.05 and assuming a dropout rate of 15%.

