### Data analysis

The categorical variables will be presented as frequencies and percentages (%) while the continuous variables will be reported as means and SDs. Patients in the intervention and control groups will be compared on an intention-to-treat basis. To assess the intervention effect, we will compare changes observed in each of the groups using Chi-square tests for categorical variables, and Student’s t-tests for continuous variables in the two independent groups, for each of the repeated measurements. To adjust variables that may confound or moderate the effect of the intervention, we will perform stratified analysis and multivariate regression analysis. Multilevel analysis, i.e., generalized mixed-effects models, will be used to estimate baseline and multivariate-adjusted between-group mean differences, adjusted odds ratios (AORs), and 95% confidence intervals (CIs) at the patient level, taking into account the clustered structure of data for patients for whom the intervention has been led by different individuals.

Longitudinal generalized mixed models will be used to analyse the overall trend in changes in the outcome measures taking into account the repeated measurements for each patient and also the clustered structure of data. These models will be linear for continuous variables, and logistic for categorical variables. Time will be considered in these models as a continuous variable, based on linear, quadratic or logarithmic functions, or as a categorical variable, with several correlated measurements for each individual. The least restrictive option with the best fit to the data will be chosen. The intervention, the time of measurement and intervention-time interaction will be included as fixed effects in the models. Patients and leaders will be included as random effects on the intercept and on the time slope. These models will be extended to include variables that may confound or modify the effect of the intervention, this being guided by the stratified analysis. At this stage, results will be presented as coefficients with their respective 95% confidence intervals. The analysis will be performed using SAS v. 9.2, SPSS v. 19 and R.

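### Two analyses of the intervention effect are listed with no stated order, and the one introduced as assessing the effect ignores clustering: nominal 5% becomes about 7.7% on the plan's own inputs

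*Protocol article*

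**What the plan says.** Three parts of the protocol article bear on this.

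- **Sample size.** The trial is sized "to detect a clinically relevant difference of 0.5% in HbA1c levels at 12 months". The calculation allows for correlation within courses: "Considering an intra-class correlation of 0.05 [18] and an average of 10 participants per group".
- **Data analysis, simple tests.** The sentence that opens the comparison of the arms, and states its purpose as assessing the effect, names Chi-square tests for categorical outcomes and Student's "t-tests for continuous variables in the two independent groups, for each of the repeated measurements". It covers every follow-up visit, so it includes HbA1c at 12 months.
- **Data analysis, models.** The same paragraph then plans multilevel models for between-group differences, odds ratios and 95% confidence intervals, "taking into account the clustered structure of data for patients for whom the intervention has been led by different individuals". The next paragraph adds longitudinal mixed models with patients and leaders as random effects.

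No sentence ranks these analyses or says which one answers the primary question.

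**The concern.** Patients are randomised individually, but those in the intervention arm then share a course of 8 to 15 people and a pair of leaders. If results vary by course, patients within a course are correlated, and a t-test that assumes independence uses too small a standard error. The article accepts this correlation when it sizes the trial and when it describes its models. It nevertheless introduces the effect comparison with tests that are valid only without it.

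The primary question can therefore receive two answers with different error rates. If the t-test were significant and the mixed model were not, the article gives no rule for which result stands. The error runs towards a false positive. The Discussion part of the abstract says that an effective programme should be spread to the whole diabetic population of the region.

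**Working it through.** **Inputs from the article.** Difference 0.5 and SD 1.5 ("we used an SD of 1.5% to calculate the sample size"); "with 80% power, with p-value of 0.05"; intra-class correlation 0.05; average group size 10; dropout 15%; 277 per arm (all Sample size). Groups of 8 to 15 come from the Intervention group section. Usual care, with no group sessions described, comes from the Control group section. Sidedness is not stated; two-sided is assumed.

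**Step 1: the plan's own figure.**
- Without clustering: n = 2 × (1.96 + 0.84)² × 1.5² / 0.5², which rounds up to 142 per arm.
- Design effect implied by the inputs: 1 + (10 − 1) × 0.05 = 1.45. The article does not print it.
- 142 × 1.45 = 206; 206 / 0.85 = 243 per arm (237 if multiplied by 1.15).

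The stated 277 is not reproduced. It is larger than 243, and well above the 168 (142 / 0.85) that would do without clustering, so an allowance for clustering is evidently intended.

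**Step 2: type I error of the t-test.** With equal arms and clustering in the intervention arm only, the true variance of the difference exceeds the variance the t-test assumes by the ratio (design effect + 1) / 2. The actual error rate is 2 × [1 − Φ(1.96 / √ratio)].

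| Correlation | Group size | Design effect | Ratio | Actual type I error |
|---|---|---|---|---|
| 0.05 | 10 | 1.45 | 1.225 | 7.7% |
| 0.05 | 8 | 1.35 | 1.175 | 7.1% |
| 0.05 | 15 | 1.70 | 1.350 | 9.2% |
| 0.01 | 10 | 1.09 | 1.045 | 5.5% |

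A simulation of 40,000 trials (24 groups of 10 against 240 ungrouped controls, correlation 0.05) gives 7.5%, in line with the first row.

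**Step 3: which results would change.** √1.225 = 1.107, so the t-test's standard error is about 10% too small (1 / 1.107 = 0.90). To be significant at a true 5%, the unadjusted statistic must reach 1.96 × 1.107 = 2.17, a nominal p of about 0.03. Unadjusted p-values between about 0.03 and 0.05 are those affected.

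**Step 4: can the trial afford the correct analysis?** Completers: 277 × 0.85 = 235 per arm.
- Unadjusted standard error: 1.5 × √(2 / 235) = 0.138, so a 95% half-width of 0.27.
- Allowing for clustering in the intervention arm: 0.138 × 1.107 = 0.153, half-width 0.30.
- Power for 0.5 is then Φ(0.5 / 0.153 − 1.96), about 90%. Even with 1.45 applied to both arms it is about 85%.

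**The case against.** The strongest reply is that the right model is already in the plan, in the same paragraph, and that it is the stated source of the estimates and confidence intervals. That is correct, and it rules out some stronger readings that a reader might infer:

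- *That the plan ignores clustering.* It does not; two sets of mixed models address it.
- *That the confidence intervals will be too narrow.* The article attaches 95% intervals only to the models. It promises none for the t-tests.
- *That the error rate is 10.4%.* This is 2 × [1 − Φ(1.96 / √1.45)] and needs separate clusters in both arms. Controls are individually randomised to usual care without groups. Correlation from shared centres would be balanced by individual randomisation; a simulation of that case gives 5.0%.
- *That the rate is higher still because leaders run several courses.* The article does not say how many courses a leader pair runs, nor that the per-group correlation carries over to a leader.

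Two further points stand. The correlation of 0.05 comes from a cited source that cannot be checked here. Also, the 7.7% describes courses whose effects differ but average to zero; if the course affected nobody, individual randomisation would keep the t-test at its nominal level.

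It can also be said that a condensed article may leave the ranking of analyses to an analysis plan. Silence on ranking alone would not be a finding. But the article does more than stay silent: it positively assigns the assessment of the effect to tests that contradict its own correlation assumption. The models do not clearly displace them either. The longitudinal models are aimed at the overall trend, their time function is chosen by fit and their covariates are guided by a stratified analysis. That leaves the t-test as the most fully fixed 12-month comparison on the page.

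**Conclusion.** The point holds in a limited form. The article lists two competing analyses of the intervention effect, does not say which decides HbA1c at 12 months, and gives the role of assessing the effect to the one that ignores clustering. On the article's own inputs the t-test's nominal 5% is about 7.7%, with a range of 7.1% to 9.2% over the planned group sizes and about 5.5% if the correlation is only 0.01. The inflation is moderate.

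The figures assume a two-sided test, equal total variance in the two arms, clustering in the intervention arm only, and a correlation that applies to change in HbA1c within courses. The design effect of 1.45 is derived from the stated correlation and group size and does not reproduce 277 per arm. Because 277 exceeds the 243 that those inputs require, nothing here shows the trial to be too small.

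**What to change.** Amend the Data analysis section in three places:

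1. Name the cluster-adjusted mixed model for HbA1c at 12 months as the single primary analysis, with the group or leader random effect applying to the intervention arm, since controls attend no course.
2. State that tests of the secondary outcomes also come from clustered models, linear or logistic as already planned.
3. Keep the t-tests and Chi-square tests if wanted, but label them unadjusted and descriptive, not tests of effect. They need not be deleted.

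This is a few sentences and needs no new data, because the model is already planned. The cost is an interval about 11% wider (half-width roughly 0.30 instead of 0.27 at 235 completers per arm). The planned 277 per arm absorbs that with power still above the 80% target.

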## Background

Managing patients with chronic health problems represents a challenge for health services. According to the 2007 Basque Health Survey, chronic diseases are increasingly prevalent in our setting, currently, 83.5% of women and 86.1% of men aged over 65 years having some type of chronic condition [1]. In the health system, 80% of primary care consultations are related to chronic diseases, as 60% of hospital admissions and 70% of health expenditure [2].

In particular, the incidence of type 2 diabetes mellitus (DM2) has increased in our region in recent years. Indeed, it is predicted that prevalence of DM2 may reach up to 12% in the population over 30 years of age [3]. Mortality and morbidity in DM2 patients are known to be much higher than those in the general population; specifically, in diabetic patients, the mortality rate ranges from 13 to 30 deaths per 100,000 people per year, and 75% of these deaths are due to heart disease [3]. Further, it has been estimated that diabetes accounts for as much as 6.3 to 7.4% of health expenditure in our health system, while 42% of people with diabetes in our region are obese, 79.6% have high blood pressure and 22% have diabetic macroangiopathy [4]. According to the latest internal assessment data, there is room for improvement in diabetes control in our setting. Well-controlled diabetic patients, that is, those with HbA1c levels below 7%, represent just 44% of the overall diabetic population, and blood pressure is under 140/90 in only 25% of patients (unpublished data from internal assessments in the Basque Health Service, Osakidetza).

Health systems need to provide more efficient and coordinated care to patients with chronic conditions and this should be focused on decreasing rates of deterioration and improving the quality of life of patients and their families/caregivers. In relation to this, primary care has an essential role [2]. As in other developed countries, the Spanish Health System is outdated, and a new organisational model is needed to respond to the challenge of providing care to chronic patients [5]. Though several models have been proposed, the Chronic Care Model and the Kaiser Permanente model are among the most used and studied [2].

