#### Secondary outcome measures

Changes in the following:

● Body weight, height and BMI measured in standard conditions

● Systolic and diastolic blood pressure (SBP and DBP) measured by a validated automated sphygmomanometer following the recommendations in the 2007 Osakidetza clinical practice guidelines [14]

● Total and HDL cholesterol levels

● REGICOR cardiovascular risk scores [15]

● Quality of life assessed by the Spanish version of the ADDQoL-19 [16]

● Self-efficacy assessed using the Diabetes Self-efficacy Scale from Stanford University, and the level of physical activity assessed by the 7-day Physical Activity Recall (PAR) [17] questionnaire

● Mediterranean-Dietary Quality Index (PREDIMED Study)

● Medication taken for DM and associated risk factors (hypoglycaemic, antiplatelet, antihypertensive and lipid-lowering medication)

● Daily expenditure on medication

● Use of health services (number of visits to the doctor or nurse, admissions due to diabetes-related metabolic decompensation)

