#### Independent variables

Age; sex; number of years since diagnosis of diabetes; history of diabetic microvascular disease: retinopathy, nephropathy or neuropathy; history of diabetic macrovascular disease: heart disease, peripheral arterial disease or cerebrovascular accident; treatment with anti-hyperglycaemic drugs: oral hypoglycaemic agents or insulin; and preventive cardiovascular medication: antiplatelet, antihypertensive and lipid-lowering drugs.

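### Adjusters and effect modifiers for the longitudinal models are to be chosen from the stratified results; they should be fixed beforehand, at baseline values

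*Protocol article*

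**What the plan says.** The Data analysis section of the protocol article has three layers.

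- **Unadjusted comparison at each visit:** "we will compare changes observed in each of the groups using Chi-square tests for categorical variables, and Student’s t-tests for continuous variables".
- **Multilevel models**, which "will be used to estimate baseline and multivariate-adjusted between-group mean differences", allowing for clustering by leader.
- **Longitudinal mixed models** with arm, time and their interaction. The selection rule stands here: "These models will be extended to include variables that may confound or modify the effect of the intervention, this being guided by the stratified analysis".

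An earlier sentence, "To adjust variables that may confound or moderate the effect of the intervention, we will perform stratified analysis and multivariate regression analysis", puts confounding and moderation under one head and names no variables. The section does not say which layer is primary.

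The section Independent variables lists age, sex, diabetes duration, microvascular and macrovascular history, and drug treatment. The treatment entry includes "treatment with anti-hyperglycaemic drugs: oral hypoglycaemic agents or insulin", with no time point. Baseline HbA1c is not on that list. Secondary outcome measures, which are changes, include "Medication taken for DM and associated risk factors", covering the same drug classes.

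The sections Recruitment process, Randomisation and Outcome variables all place baseline measurement before allocation. Limitations of the study relies on randomisation to make the arms comparable.

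**The concern.** A stratified analysis of the intervention effect is an analysis of outcome data. If it decides which variables enter the model, the adjusted estimate and the reported modifiers are both chosen with results in view. That procedure belongs to observational studies, where confounders have to be found. Here allocation is random, so systematic confounding by baseline characteristics is not expected. Adjustment serves precision and deals with chance imbalance, and neither purpose needs outcome results to pick the covariates.

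Two things are at stake. Strata that differ by chance may be reported as real effect modifiers. And several adjusted estimates will exist, with nothing in the article to say which one counts.

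Medication adds a narrower risk. The programme's impact on prescribing is a secondary objective, so drug use after randomisation may itself be an effect of the intervention. The listed covariate is not restricted to its baseline value.

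**Working it through.** The plan gives no figure on this point, so there is none to reproduce. All simulation settings below are assumptions, not figures from the article.

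**1. False effect modifiers**

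The Independent variables section can be counted in two ways.

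- Separately: 3 (age, sex, duration) + 3 microvascular + 3 macrovascular + 2 glucose-lowering + 3 preventive = 14.
- Grouped: age, sex, duration, microvascular, macrovascular, glucose-lowering, preventive = 7.

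With independent tests at 0.05 and no true modifier, P(at least one) = 1 − 0.95^k.

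- k = 7: 1 − 0.95^7 = 0.302
- k = 14: 1 − 0.95^14 = 0.512

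Simulation gave 30% and 51%.

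**2. Type I error of the main effect**

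The number analysed per arm is 277 × 0.85 = 235 (Sample size section). The simulation used 2,000 runs with no true effect, independent binary baseline covariates (prevalence 40%, effect 0.3 each), residual SD 1.4 and no clustering.

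| Rule | 7 variables | 14 variables |
|---|---|---|
| Unadjusted | 5.7% | 5.3% |
| Keep covariates that move the estimate by more than 10% | 5.1% | 5.3% |
| Keep only covariates that move the estimate toward benefit | 5.9% | 8.9% |

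Under the last rule the mean estimate shifted by −0.04 (7 variables) and −0.08 (14 variables) HbA1c points. Under the neutral rule it stayed at about 0. The Monte Carlo standard error near 5% is √(0.05 × 0.95 / 2000) = 0.5 percentage points. So 5.9% is hardly distinguishable from 5%, while 8.9% clearly is.

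**3. Medication as a covariate**

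This simulation assumed a drug effect of −0.5 points and an intervention that shifts drug use by 10 percentage points either way.

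- Adjusting for baseline medication: bias 0.004 or less.
- Adjusting for follow-up medication: bias +0.015 (use shifted down) or −0.018 (use shifted up), and about 0 when use does not shift.

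The small bias reflects two opposing parts. With use shifted down, blocking the drug pathway alone would change the estimate by −0.5 × 0.10 = −0.05. The net +0.015 therefore implies about +0.065 from comparing patients of unequal severity at the same drug status. Other settings need not cancel so closely.

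**4. Power of one pre-specified modifier, baseline HbA1c**

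The Background section says that "those with HbA1c levels below 7%, represent just 44% of the overall diabetic population". If trial patients split the same way, there are 0.56 × 235 = 132 per arm at or above 7% and 0.44 × 235 = 103 per arm below. Assume SD 1.5 in each stratum and effects that differ by 0.5 points, and ignore clustering.

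- SE = 1.5 × √(2/132 + 2/103) = 0.279
- Power = Φ(0.5/0.279 − 1.96) = Φ(−0.17) = 0.43

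**The case against.** The strongest reply is that a condensed article need not name its covariates, and that the extended models come after unadjusted comparisons which no selection can touch. Both statements are correct. The t-test on changes is unaffected, and the lack of a named covariate list would be no finding. The article is not silent, however: it states a selection rule, and the rule depends on results.

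Several stronger readings are tempting, and the document does not support them.

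- **The p-value is invalid.** A reader might infer this from selection on outcome data. A neutral rule kept the error at 5.1% to 5.3%. Only selection that favours benefit raised it, and nothing in the article suggests that intention.
- **Baseline HbA1c is left out of the analysis.** It is absent from the Independent variables list, but Data analysis announces baseline-adjusted differences, the primary outcome is a change, and baseline is one of the four measurements. Nothing excludes it from the stratified analysis either. Leaving it out of a randomised comparison would cost precision, not cause bias.
- **Medication is contradictory as both covariate and outcome.** Treatment at entry and change in treatment are different quantities, and the list reads naturally as patient characteristics. At its baseline value medication is a legitimate covariate. The defect is only the missing time point.
- **The effect will be diluted by well-controlled patients.** That needs an assumed lack of benefit below 7%. It also applies a figure for the overall diabetic population to trial volunteers, and it does not measure the selection problem.

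It also stands that the article never names the Independent variables section as the candidate list and states no 0.05 screen.

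**Conclusion.** The concern holds in limited form. The article lets outcome results choose the adjusters and effect modifiers of the longitudinal models, and that rule should be replaced.

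The firmer harm is false modifiers: a 30% to 51% chance of at least one, conditional on the assumed screen, independent tests and the inferred candidate list. The second is a free choice among adjusted estimates. It is harmless to the type I error under a neutral rule and raises it to about 6% to 9% if selection favours benefit. Only the 14-variable figure is clearly above 5%.

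Medication calls for a clarification. Bias arises only if follow-up values are used and the intervention changes drug use. It was about 0.02 points in the settings tried, against a target difference of 0.5, but that figure is not an upper bound.

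**What to change.** In Data analysis, replace the clause that lets the stratified analysis guide model extension with wording to this effect:

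- The covariate set is fixed before outcome data are seen and uses pre-randomisation values only. Baseline HbA1c is named explicitly, and any medication covariate is taken at baseline.
- Nothing measured after randomisation enters the model for the intervention effect.
- A short, pre-specified list of modifiers is tested by interaction with arm. Baseline HbA1c is a reasonable example, stated as supportive because its power is only about 43% on the inputs above.
- All other subgroup and stratified results are labelled exploratory.

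In Independent variables, add that drug treatment means treatment at baseline.

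The cost is analysis wording and less freedom to explore. No data collection or sample size changes.

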### Design

A randomised clinical trial will be carried out in four health regions of the Basque Health Service (Araba, Gipuzkoa, Ezkerraldea-Enkarterri and the Bidasoa Integrated Health Organisation) involving a total of 556 DM2 patients between 18 and 79 years old, recruited proactively, as described in the section on the recruitment process below. Patients will be randomly assigned to intervention and control groups, and will be followed up over two years. Measurements will be taken at four time points: baseline, and 6, 12 and 24 months after the intervention. The research protocol has been approved by the Basque Country Clinical Research Ethics Committee (Ref. no.: 11/2010).

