### Randomisation

Randomisation will be performed centrally by staff other than those of the research team, using a computer-generated random number sequence and after taking the baseline measurements.

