### Outcome variables

Baseline measurements will be taken prior to randomisation. As noted above, the clinical data will be collected at each health centre by collaborating health professionals, previously trained by the research team. Some instruments to be used are for self-completion by patients, while others are questionnaires for use by interviewers previously trained by the research team.

Blood samples will be collected by staff at the patients’ assigned health centres, and the analysis will be performed at the reference laboratories of the four participating health regions.

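### The HbA1c mixed models name leader and patient but not health region; if HbA1c change differs between regions, their interval is slightly too wide, which one sentence would prevent

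*Protocol article*

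**What the plan says.** The Design section sets the trial in four regions: "A randomised clinical trial will be carried out in four health regions of the Basque Health Service". The Randomisation section describes central allocation of individual patients and mentions no regional stratification: "Randomisation will be performed centrally by staff other than those of the research team, using a computer-generated random number sequence". On the assay, Outcome variables says "the analysis will be performed at the reference laboratories of the four participating health regions". The primary outcome is the change in HbA1c.

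The Data analysis section names the model terms. The multilevel model works by "taking into account the clustered structure of data for patients for whom the intervention has been led by different individuals". For the longitudinal model the fixed part is "The intervention, the time of measurement and intervention-time interaction will be included as fixed effects in the models" and the random part is "Patients and leaders will be included as random effects on the intercept and on the time slope". An open clause follows: "These models will be extended to include variables that may confound or modify the effect of the intervention, this being guided by the stratified analysis".

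The Independent variables section begins "Age; sex; number of years since diagnosis of diabetes" and continues with vascular history and medication. Region is not in it.

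**The concern.** Region is a design factor shared by both arms. It determines the laboratory and, presumably, which leaders a patient can meet. Because patients are randomised individually, a regional difference in HbA1c change is expected in both arms and should cancel from the treatment contrast.

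The named terms do not let it cancel fully in the reported standard error. Only intervention patients have leaders. If each leader works in one region, leaders in the same region share that region's deviation, and a model without region reads this as variation between leaders. It then carries the variation into the uncertainty of the treatment effect. In the control arm the same deviation goes into patient or residual variance, where it matters far less. At stake is some precision in the mixed-model estimate.

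**Working it through.** **Inputs from the Sample size section:** SD 1.5, ICC 0.05, 10 participants per group, difference 0.5, 277 per arm, 15% dropout, 80% power, p-value 0.05 (two-sided assumed).

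**The plan's own figure.** 2(1.960 + 0.842)² × 1.5²/0.5² gives 142 per arm. Times the design effect 1 + 9 × 0.05 = 1.45 gives 206, and divided by 0.85 gives 243. The stated 277 is not reproduced at 80% power; at 85% power the same steps give 162, 234.9 and 277. That is a separate matter. The check below takes 277 as it stands: 277 × 0.85 = 235.45 analysed per arm, in about 277/10 ≈ 28 courses.

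**Assumptions not in the documents:** between-region SD of HbA1c change t = 0.1 to 0.3; each leader works in one region; one leader unit per course; leader clustering in the intervention arm only; SD 1.5 applies to the analysed change.

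**1. Closed form.** Without regional differences:

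- variance = 2.25 × (1.45 + 1)/235.45 = 0.0234, SE 0.153, power for 0.5 about 90.5%. This exceeds the planned power mainly because only one arm is inflated for clustering.

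Without a region term, the added variance is t²/28 + t²/235.45:

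- t = 0.1: 0.0004, SE 0.154, power 90.0%
- t = 0.2: 0.0016, SE 0.158, power 88.5%
- t = 0.3: 0.0036, SE 0.164, power 86.0%

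**2. Four-visit model, change from baseline to 12 months.** Complete data, 240 per arm, 24 leaders, residual variance 1.0, leader slope variance 0.05 (the last two assumed):

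- variance = 4 × 1.0/240 + (0.05 + t²)/24
- SE = 0.1369 at t = 0, then 0.1384, 0.1429 and 0.1500 at t = 0.1, 0.2 and 0.3

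**3. Stable offsets.** In the same model without leader slope variance, a regional SD of HbA1c level of 0, 0.2, 0.3 or 0.5 leaves the SE of change at 0.1291 with complete data, and at 0.1338 with 15% dropout. Constant laboratory differences do not widen the interval for change.

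**4. REML simulations** (four regions, about 235 per arm, reported SE without/with fixed region).

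| Region SD | Closed form | Four-visit change model | Simulation, 200 trials per setting | Simulation, 1,500 trials per setting (single 12-month value) | Further simulation of change |
|---|---|---|---|---|---|
| 0 | – | – | 0.1513/0.1516 | 0.1520/0.1524 | 0.149/0.150 |
| 0.1 | +0.8% | +1.1% | – | 0.1534/0.1524 (+0.7%) | 0.150/0.150 (0%) |
| 0.2 | +3.4% | +4.3% | 0.1550/0.1512 (+2.5%) | 0.1572/0.1519 (+3.5%) | 0.152/0.149 (+2.0%) |
| 0.3 | +7.4% | +9.5% | 0.1577/0.1506 (+4.7%) | 0.1642/0.1524 (+7.7%) | 0.156/0.149 (+4.7%) |

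In the 1,500-trial simulation at SD 0.3, the estimated leader variance rose from 0.12 to 0.20. The actual spread of the two estimates was almost the same (0.1530 and 0.1519), while coverage was 96.7% without region and 94.5% with it. The gain is therefore a correctly sized standard error, not a better point estimate.

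**5. Effect varying by region.** With a treatment effect that differs between regions at SD 0.2, and inference to regions in general, coverage was 90-91% both with and without a region main effect.

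**The case against.** **Region is not excluded.** The Data analysis section allows multivariate adjustment and extension of the models, the Independent variables list is not declared closed, and a final covariate list often sits in an analysis plan that is not shown here. This stands in part: it would be wrong to say that the plan rules region out. But the extension clause is for confounders or modifiers found through the stratified analysis. That is a data-guided route, not advance inclusion of a design factor, and the model terms that the article does name omit region.

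**The widening is conditional.** A reader might infer that four laboratories make the interval too wide as a matter of fact. The documents do not support that. The outcome is change, and stable offsets cancel (step 3). Nothing in the article says that HbA1c change differs by region, and the Control group section points to common primary care protocols. Nesting of leaders in regions is plausible for local weekly sessions but is not stated, nor is the number of leaders. All of this stands, and the point is worded accordingly.

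**The size is small.** A reader might also infer a serious loss of power. The closed form drops by 8 points (90.5% to 82.5%) only at a regional SD of change of 0.4. That variance, 0.16, exceeds the whole cluster variance implied by the plan, 0.05 × 2.25 = 0.1125, and even then power stays above the planned 80%. If the cited ICC already contains regional variation, the planning SE of 0.153 is not exceeded at all, and the region term would simply bring the SE below it.

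**Scope.** The Student's t-tests on changes contain no leader variance, so this mechanism does not touch them.

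**Conclusion.** The point holds as a minor one about precision. The named HbA1c mixed models omit a design factor common to both arms. If HbA1c change differs between regions and leaders work within one region, the reported standard error is too large by about 0-1% at a regional SD of change of 0.1, 2-4% at 0.2 and 5-10% at 0.3. All three SDs are assumed, since the documents give none.

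The error is conservative. It does not bias the estimate or raise the false-positive rate. Nor do the simulations support a reading that uncorrected regional imbalance harms the estimate: its true spread barely changed when region was added.

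**What to change.** In Data analysis, state that health region enters the HbA1c mixed models as a fixed effect together with its interaction with time, and keep the leader random effect. Add region to the list under Independent variables. Naming it in advance also removes a later choice about whether to adjust for it.

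The cost is one sentence and one list entry. Region is known for every patient, since eligibility requires belonging to one of the four. It uses 3 degrees of freedom per time point out of about 2 × 235 = 470 analysed patients. With no regional differences the simulated SE was virtually unchanged (0.1513 without, 0.1516 with region).

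The change does not deal with a treatment effect that itself varies by region. If that is of interest, it needs its own term and a statement of whether inference is to these four regions or to regions in general.
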